#### Weekly outcomes

The 8-item Children’s Anxiety Scale (CAS-8) [61]. The CAS-8 is a short version of the SCAS containing 8 items. I has shown acceptable psychometric properties, with good reliability [61].

The Short Mood and Feelings questionnaire (S-MFQ) [62]. The S-MFQ is a short version of MFQ, at shows high accuracy for discriminating MDD cases from non-cases [63].

Sociodemographic measures will be gathered on parents regarding age, level of education, job status, civil status, gender, and primary caregiver in case of single parents. For the adolescents, information will be gathered regarding age and gender.

### Participant timeline {13}

All participants will need to register through a website to participate in the project. During registration, participants will be required to complete an initial screening questionnaire to assess exclusion criteria. If an exclusion criterion is met, the participant will automatically be informed within the questionnaire that they are unable to participate and will be given the choice to either continue or discontinue their application process.

Participants who complete the screening questionnaire and who are not excluded are invited to participate in a video call with one of the research staff members, during which they will receive information about the study, their rights, and a consent form. Participants will have the option to verbally consent to participation during the video call, or they may be prompted to schedule another time to clarify their participation.

Participants who provide both written and verbal consent will receive an online questionnaire package. For adolescents, this package will include the following assessments: The Youth Online Diagnostic Assessment (YODA), Spence Children’s Anxiety Scale (SCAS), Child Anxiety Life Interference Scale (CALIS), The Mood and Feelings Questionnaire (MFQ), and EuroQol-5 Dimension Youth (EQ-5D-5L). For parents, the package will include the caregiver version of YODA, SCAS-C/P, MFQ, and CALIS.

After completing the questionnaires, participants will be invited to a video call with a clinical psychologist for an assessment interview. Based on the collected data and the assessment interview, the clinical psychologist will determine if the participant meets the diagnostic criteria for an anxiety diagnosis according to DSM-5, and are eligible to take part in the study. If eligible, the participant will be randomized in to the three conditions. If the participants are in the two treatment conditions they will be provided with login credentials for the treatment platform. If the participants are in the waitlist, the will be notified that they will get the login credentials after answering the post-waitlist questionnaires.

Participants and their parents will engage in the treatment for 14 weeks. They will have access to the platform for an additional 12 weeks after end of the treatment period. After 10 weeks of active participation in the treatment, the participants in the intervention conditions will be randomized to either receive a post-treatment booster session or not. Participants allocated to the booster condition will gain access to the booster module 24 weeks after receiving their login.

Immediately after the 14-week treatment period, participants will be assessed with post-treatment questionnaires and invited to a final video call with the clinical psychologist to conclude the active part of treatment.

Follow-up measurements will be conducted 3, 6, and 12 months after completing the treatment (Table 3).

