### Objectives {7}

The primary aim of the study is to examine the effectiveness of CoolMinds, an Internet-delivered cognitive behavioral therapy intervention, among adolescents aged 12–17 years. Specifically, the study seeks to examine the effectiveness of CoolMinds when administered with either planned feedback or on-demand feedback from a therapist, compared to a waitlist control group. Furthermore, the study will explore the effectiveness of delivering one booster session compared to no booster session in enhancing treatment outcomes.

We hypothesize that a higher proportion of participants in the two treatment conditions will achieve recovery from their primary anxiety diagnosis compared to those in the waitlist control group. Additionally, both treatment conditions are hypothesized to result in greater reduction in anxiety symptoms compared to the waitlist control group. We also hypothesize that the booster session will increase and better maintain reduction in anxiety symptoms over time.

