#### Secondary outcomes

The secondary outcomes consists of point differences in anxiety diagnosis and severity measured by clinician-review Youth Online Diagnostic Assessment-Child and Parent Versions (YODA) [48]. YODA is an online diagnostic assessment tool that assesses DSM-5 anxiety disorders and specific phobias based on the *Anxiety and Related Disorders Interview Schedule for DSM-5*, which is considered the golden standard [49]. The YODA uses yes/no responses to closed-ended questions, as well as open-ended questions that require written descriptions of cognitions, behaviors and impact on functioning [48]. The YODA is completed separately by the adolescent and the parents, and a clinical psychologist trained in the assessment of adolescent anxiety disorders then reviews and evaluates the responses to determine the diagnosis and symptom severity.

Point differences in anxiety symptoms interference on daily life measured by the self- and parent-reported questionnaire Child Anxiety Life Interference Scale (CALIS) [46]. CALIS [50] is used to measure the impact of youth anxiety on various areas of life functioning such as school, extracurricular activities, family life and friendships. The impact is evaluated separately by adolescents and their parents. In addition, parents rate the degree of impact on their own lives. CALIS has shown satisfactory internal consistency and moderate test-retest reliability [50].

Point differences in depressive symptoms are measured by The mood and Feelings Questionnaire (MFQ) [51]. MFQ is used to screen for depression in youth, both in epidemiological samples and in clinical samples, it is recommended as a self-report screening tool in secondary care [51]. The MFQ is completed separately by the adolescent and a parent. The MFQ has been validated in a Danish population sample of adolescents and shown excellent internal consistency [52].

Point differences in Quality of life is measured by EuroQol-5 Dimension Youth (EQ-5D-5L) [52], a 5-item self-report questionnaire assessing quality of life and self-rated health. The items cover five domains: mobility, self-care, usual activities, pain/discomfort, and anxiety and depression [53].

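### The entry diagnosis uses a video interview, but the outcome diagnosis is described as a review of YODA responses, so counted recovery may mix true change with a change of method

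*Protocol article*

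**What the plan says.** **Entry (Participant timeline {13}).** YODA is part of the questionnaire package given before randomisation: "For adolescents, this package will include the following assessments: The Youth Online Diagnostic Assessment (YODA"; parents complete the caregiver version. A clinician contact follows: "After completing the questionnaires, participants will be invited to a video call with a clinical psychologist for an assessment interview". The decision then uses both sources: "Based on the collected data and the assessment interview, the clinical psychologist will determine if the participant meets the diagnostic criteria".

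**Outcome (Secondary outcomes).** Adolescent and parents complete YODA separately, and a trained psychologist "then reviews and evaluates the responses to determine the diagnosis and symptom severity". This passage mentions no interview, and no diagnostic interview is described elsewhere after baseline.

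**End of treatment (Participant timeline {13}).** After the post-treatment questionnaires, participants are "invited to a final video call with the clinical psychologist to conclude the active part of treatment". No equivalent call is described for the waitlist, whose participants answer the post-waitlist questionnaires and then receive their login.

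**Hypothesis and analysis.** Objectives {7} expects that "a higher proportion of participants in the two treatment conditions will achieve recovery from their primary anxiety diagnosis", against waitlist. Section {20a} compares YODA, dichotomised at a total score of 1, between the three conditions at post-treatment by logistic regression. It mentions no baseline YODA term.

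**Blinding {17a}.** Clinicians and the research team are not blinded. The only stated mitigation is that the data are pseudonymised for analysis.

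**The concern.** Recovery is a statement about change, and change is interpretable only if both ends are measured in the same way. Here the diagnosis from which an adolescent is to recover draws on an interview, while the diagnosis that decides recovery is described without one.

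An adolescent with brief or minimising written answers might be admitted because the interview brought out more. The same written answers at week 14 could be rated as no diagnosis although nothing has changed. The opposite error is also possible: written answers reviewed without an interview may be over-read, so that a real recovery is missed.

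The second issue is the order of steps. The document does not say whether the YODA rating is completed before or after the closing call. If after, the rater of an iCBT participant can draw on a conversation that is not described for waitlist participants. This is separate from masking: a rater who did not know the allocation would still have unequal material to judge from.

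At stake are the recovery proportions that readers will quote and, if the order of steps differs by arm, the randomised comparison itself.

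**Working it through.** **No plan figure to reproduce.** The document gives no recovery rate, no YODA-to-interview agreement rate and no power for YODA. Its sample size of 134, raised to 168 for 20% attrition (134/0.8 = 167.5), is for SCAS and does not bear on this point.

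**Step 1: the two procedures side by side.**

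| | Entry | Post-treatment |
|---|---|---|
| YODA, adolescent and parent | yes | yes |
| Other questionnaires feed the diagnosis | yes | not described |
| Assessment interview | yes | not described |
| Other psychologist call | – | closing call, described for treatment only; role in rating not stated |

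**Step 2: same procedure in all arms, YODA-negative entrants.** Assumptions: true recovery is p; a share d of entrants is interview-positive but YODA-negative at baseline, and all of them stay YODA-negative. Then

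observed recovery = d + (1 − d)p, and observed difference = (1 − d) × true difference.

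With p = 20% (waitlist) and 50% (iCBT), both assumed:

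| d | Waitlist | iCBT | Difference | Power |
|---|---|---|---|---|
| 0 | 20% | 50% | 30 points | 0.94 |
| 5% | 24% | 52.5% | 28.5 | 0.90 |
| 10% | 28% | 55% | 27 | 0.86 |
| 20% | 36% | 60% | 24 | 0.76 |
| 30% | 44% | 65% | 21 | 0.65 |

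Power is a two-sided 5% normal approximation for two proportions, with the 134 split 1:2 and rounded to 45 and 90, iCBT arms pooled. With p = 20% and 40%, d = 10% gives 28% v 46% (18 points instead of 20) and d = 20% gives 36% v 52% (16 points).

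At d = 10% and p = 20%/50%, the artefact share of counted recovery is (28 − 20)/28 = 29% in the waitlist and (55 − 50)/55 = 9% in iCBT. At d = 0 there is none.

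**Step 3: same procedure, opposite error.** Suppose the YODA review still assigns a diagnosis to a share f of those who truly recovered. Then observed recovery = p(1 − f). With f = 10%, 20% becomes 18%, 50% becomes 45%, and the difference is again 27 points. Within-arm rates now move down instead of up. In both cases the contrast shrinks. If true recovery is equal in the arms, observed recovery is equal too, so no effect is created.

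**Step 4: procedure differs by arm.** Suppose the closing call restores interview-type information in iCBT only, so that iCBT shows p and waitlist shows d + (1 − d)p. With d = 10%, the rates are 50% v 28%, a difference of 22 points. With no true effect (20% in both) they are 20% v 28%, a spurious −8 points. If instead the call inclines raters towards recovery in iCBT, the error has the opposite sign. Unlike Steps 2 and 3, this case can create a difference where there is none.

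**The case against.** **A reader might infer that the outcome rests on YODA alone.** The document does not say so. The instrument is described once, for no particular time point, as a psychologist's review rather than an automatic score. The timeline table and flow figure are not shown, the article is condensed, and a field guidebook holds the step-by-step instructions. This stands: the mismatch is in what is described, not in a stated rule.

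**A reader might infer that part of the counted recovery is certainly artefact and that rates are inflated in every arm.** This is not supported. The share d is unknown and may be near zero, child and parent versions may compensate for each other's gaps, and Step 3 shows that the error can run the other way.

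**The planned comparison is largely protected.** Section {20a} compares YODA status between randomised arms. Entrants who are interview-positive but YODA-negative are fixed before randomisation, so they are balanced in expectation. This stands for a procedure common to all arms, where the cost is dilution.

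**The closing call may never reach the rating.** Questionnaires are listed before the call, and nothing says that the call informs the diagnosis. This stands as far as it goes, but when the questionnaire is completed does not settle when the psychologist rates it.

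**The definition of recovery can be left to the analysis plan.** That is so for the definition and the model. It does not cover the order of rating and clinician contact, which is trial conduct: a later analysis plan cannot equalise ratings made on unequal information.

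**Re-rating or dropping participants brings its own bias.** This stands. Unblinded retrospective rating, or a denominator limited to baseline YODA-positives as the main analysis, would be worse than the present whole-sample comparison. The fix takes account of it.

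**Conclusion.** The point holds as a mismatch in the described methods and an open question about the order of steps. Recovery counted from the entry diagnosis may mix true change with a change of method; neither size nor direction can be taken from the document.

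On the assumed 20% and 50% true recovery, a baseline discordance of 5% to 30% adds 4 to 24 points to the waitlist rate and 2.5 to 15 points to the iCBT rate, and cuts the difference from 30 to between 28.5 and 21 points. These figures rest on assumed recovery and discordance rates and on every discordant entrant remaining YODA-negative.

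With one procedure for all arms, this is distortion of within-arm rates and possible dilution, not a false treatment effect. A false effect becomes possible only if the rating follows the closing call in the iCBT arms and has no counterpart in the waitlist. The document leaves that open; it does not state it.

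The change is worth making because recovery is the first hypothesis and the correction is cheap.

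**What to change.** - **Baseline.** The psychologist records a YODA-only principal diagnosis and severity before the assessment interview. The interview-supported diagnosis continues to decide eligibility.
- **Post-treatment and follow-up.** The YODA rating is made from the written responses and locked before any closing call, by the same procedure in all three arms at post-treatment. The protocol states this order.
- **Analysis.** Keep all randomised participants in the YODA logistic regression and adjust for baseline YODA-only status or severity. Report loss of the YODA-only baseline diagnosis among baseline-positive participants as a supportive analysis, not as the main one.
- **Already enrolled.** Make any retrospective baseline rating from stored YODA responses, without sight of allocation.

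The cost is one extra recorded rating per participant, a fixed order of steps and a protocol clarification. No added visits or participants are needed. Allocation-masked rating of stored responses takes some rater time, and the supportive analysis has a smaller denominator.

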**Table 3 Tab3:**
[figure not shown]
Participant timeline

### Sample size {14}

The sample size calculation is based on scenarios of difference between treatment and waitlist at end of treatment for the primary outcome SCAS, based on Stjerneklar and colleagues [32] previous study detecting a difference of 10 points between the waiting list and the (combined) treatment groups in change in SCAS score from baseline to 3 months’ follow-up. Using a linear mixed model with outcome variance *σ*^2^=225 (*σ* = 15) and intraclass coefficient ICC=0.6 [32], and with significance level *a* = 0.05 and power = 1−b = 0.80, allowing for unequal group sample sizes (randomized 1:2), a total sample size of 134 patients is needed [64, 65]. Allowing for 20% attrition, a total of *n* = 168 patients (*n* = 56 waiting list, *n* = 112 treatment) will be included.

### Recruitment {15}

Participants will be recruited through self-referral and referral from health specialists within Denmark. The project will be promoted on Facebook and Instagram.

If social media advertisement is not sufficient, information letters will be sent to educational psychologists, general practitioners (GPs), and adolescent mental health care units. Additionally, letters will be sent to counseling services operated by volunteers and non-governmental organizations.

The recruitment will proceed until 168 participants are enrolled or until all clinicians are fully booked. If all clinicians are fully booked, recruitment will be temporarily paused until additional clinician availability becomes available.

## Assignment of interventions: allocation

### Sequence generation {16a}

The trial will use an allocation ratio of 1:1:1. Participants will be stratified by age in two categories 12–14 years of age and 15–17 respectively. Block randomization will be used with variable block sizes. To reduce predictability of a random sequence, the block sizes are made with random block sizes in Stata version 18 [66] by a statistician, and neither the research team, the clinicians or the administrative team have access to this information at any point of the trial.

### Concealment mechanism {16b}

The random block sizes are concealed in REDCap [38, 39] by our data manager. There is not possible for the research team, the clinicians, or the administrative team to see the allocation of the participant before the intervention is assigned. The intervention is assigned using the randomization function in REDCap, it is not possible to change allocation for the participant at any time of the study as this function in REDCap is blocked by our data manager.

### Implementation {16c}

A statistician will generate the allocation sequence, the clinicians will enroll participants, and assign participants to the interventions.

## Assignment of interventions: Blinding

### Who will be blinded {17a}

Given the nature of the study examining the effectiveness of a novel format of psychotherapy and the examination of difference in therapist support, blinding participants and clinicians is not possible. Additionally, the research team actively engages in day-to-day project operations, including the screening for suicidality, and therefore, the research team is not blinded.

However, to mitigate bias, the trial results will be analyzed using pseudo-anonymized data. This means that only the ID numbers will appear on the data sheet, aiming to achieve as close to assessor blinding as possible within the research design.

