### Eligibility criteria {10}

*Inclusion criteria:* Participants must be (1) between 12 and 17 years of age (both included) and have (2) a principal anxiety diagnosis according to DSM-5 criteria, as assessed by a clinical psychologist, (3) the ability to read and write Danish, (4) Internet access, and (5) a parent (or other legal guardian) able to participate in treatment alongside the adolescent. *Exclusion criteria:* (1) diagnosed with an autism spectrum disorder, (2) an Attention Deficit Hyperactive Disorder (ADHD/ADD), (3) psychotic symptoms, (4) bipolar disorder, (5) current suicidal ideation or self-mutilating behavior, (6) current alcohol or substance abuse, (7) a moderate to severe depression (8) current eating disorder and (9) received CBT for an anxiety disorder within the past 12 months.

The eligibility criteria for clinicians performing the intervention are as follows: must have a master’s degree in clinical psychology, and be employed at either Centre for Digital Psychiatry or Center for Psychological Treatment of Children and Adolescents.

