### Interim analyses {21b}

The data monitoring committee will conduct monthly analyses to ensure that there are no significant harms related to participating in this project. The members of the data monitoring committee will all have access to these interim analyses. Termination of the trial will be decided in unison, but in case of disagreement, the final decision lies with the primary investigator.

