### Composition of the data monitoring committee, its role and reporting structure {21a}

A data monitoring committee will be established, consisting of clinicians working on the project, the project data manager, and two PhD students. The committee’s role is to ensure data quality and monitor potential negative effects of participation in the study.

It’s important to note that this committee is not independent from the sponsor, as this study is internally funded. However, the data manager, who is connected to another hospital unit, is tasked with ensuring proper data management across the hospital and thus has no competing interests in the project.

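### ID-only analysis sheets cannot mask the psychologist who sets the YODA diagnosis, and no masked rater is described, so the YODA recovery outcome is open to rater bias

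*Protocol article*

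**What the plan says.** All references are to the protocol article.

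- **Who will be blinded {17a}** states that "blinding participants and clinicians is not possible" and that "the research team is not blinded". The mitigation offered is that "the trial results will be analyzed using pseudo-anonymized data", explained as meaning that "only the ID numbers will appear on the data sheet, aiming to achieve as close to assessor blinding as possible within the research design".
- **Secondary outcomes** (under Outcomes {12}) describes the YODA as an online instrument with closed items and written free text, completed separately by adolescent and parents. It is not scored automatically: "a clinical psychologist trained in the assessment of adolescent anxiety disorders then reviews and evaluates the responses to determine the diagnosis and symptom severity".
- **Implementation {16c}** has the clinicians enrol participants and assign them to arms.
- **Participant timeline {13}** has a closing video call with the clinical psychologist straight after the 14-week treatment period.
- **Objectives {7}** puts recovery from the primary anxiety diagnosis first among the hypotheses. **Statistical methods {20a}** analyses dichotomised YODA across the three conditions at post-treatment by logistic regression, as a secondary analysis. **Additional analyses {20b}** repeats this at 3 months.

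**The concern.** A human judgement stands between what families write in the YODA and the outcome that is analysed. Bias from knowing the arm enters when that judgement is made. Replacing names with ID numbers on the analysis sheet comes later and leaves the judgement as it was. By itself it does not hide the arm from the analyst either.

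The sentence in {17a} therefore offers a measure that cannot do what it is said to approach. At stake is the YODA recovery comparison with the waitlist. If raters who know the arm lean towards calling treated adolescents recovered, the trial could report a recovery benefit that lies partly or wholly in the rating. A reader of {17a} could also credit this outcome with more protection than it has.

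**Working it through.** **Step 1: the text.** The protocol states no figure on this point, so the main check sets its sections side by side.

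| Question | What the protocol article gives | Section |
|---|---|---|
| Who sets the YODA diagnosis? | A trained clinical psychologist, from written responses | Secondary outcomes |
| Is that rater masked or independent? | Not stated; no masked rater described | whole article |
| Are clinicians or the research team blinded? | Neither | {17a} |
| What is the mitigation? | ID-only analysis data | {17a} |
| When does it act? | At analysis, after rating | {17a} |
| Do the reasons against blinding cover a separate reader of forms? | No. They are the nature of psychotherapy, the difference in therapist support, and the team's daily operations including suicidality screening | {17a} |

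The last row bears on whether the design is as close to assessor blinding as it could be. The YODA is answered online in writing and reviewed afterwards, and two centres take part (Study setting {9}). A separate psychologist could therefore read the responses without the arm. Day-to-day risk screening uses the S-MFQ and CAS-8 (Adverse event reporting {22}), so masking the YODA reader need not touch it.

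**Step 2: scale, as illustration only.** The documents give neither a recovery rate nor a rater error, so both are assumed.

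Inputs:
- Numbers assessed: 134 from Sample size {14}, split 1:2. That is 134/3 ≈ 45 waitlist and 2 × 134/3 ≈ 89 iCBT.
- True recovery p₀, the same in all arms (no effect): 10%, 20% or 30%, assumed.
- Tipping b: 5% or 10%, assumed, read in two ways. In (a), b is a share of all iCBT ratings, so apparent recovery is p₁ = p₀ + b. In (b), b is a share of the iCBT participants who are still ill, so p₁ = p₀ + (1 − p₀)b.

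Formula: chance of significance favouring iCBT = Φ[(p₁ − p₀ − 1.96·SE₀)/SE₁]. Here SE₀ = √[p̄(1 − p̄)(1/45 + 1/89)], with p̄ the pooled proportion, and SE₁ = √[p₀(1 − p₀)/45 + p₁(1 − p₁)/89].

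Worked case, p₀ = 0.20, b = 5%, reading (a):
- p₁ = 0.25 and p̄ = (45 × 0.20 + 89 × 0.25)/134 = 0.233.
- SE₀ = 0.0774 and SE₁ = 0.0752.
- (0.05 − 1.96 × 0.0774)/0.0752 = −1.35, and Φ(−1.35) ≈ 0.088.

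All cases:

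| p₀ | b = 5%, (a) | b = 5%, (b) | b = 10%, (a) | b = 10%, (b) |
|---|---|---|---|---|
| 10% | 11.0% | 9.7% | 29.3% | 24.9% |
| 20% | 8.8% | 7.1% | 22.3% | 16.0% |
| 30% | 8.1% | 5.9% | 19.8% | 11.9% |

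The range is about 6% to 11% for 5% tipping and about 12% to 29% for 10% tipping, against a nominal 2.5% in that direction.

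Two limits apply. The calculation pools the two iCBT arms, whereas {20a} names a logistic regression on three conditions. It also covers post-treatment only, because the waitlist leaves the study after that point (Trial design {8}). At 3 months the question is rater bias between the iCBT arms.

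**The case against.** The strongest reply is that {17a} is candid. It says outright that participants, clinicians and the research team are not blinded, and it speaks of aiming at something close to assessor blinding, not of achieving it. That stands: the lack of blinding is disclosed. The fault is narrower, in that the measure named cannot move the design towards the aim.

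A second reply is that no sentence says who rates the post-treatment YODA. A reader might infer that the treating clinician does, or at least another unblinded project clinician. The documents do not settle this. The requirement to "be employed at either Centre for Digital Psychiatry or Center for Psychological Treatment of Children and Adolescents" applies to clinicians who deliver the intervention, not expressly to YODA raters, and the full protocol may assign raters. What can be said is that no masked rater is described while the clinicians and the research team are declared unblinded.

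Third, masked rating would not make the YODA a blinded outcome. A reader might think it could be freed from unblinded self-report, but adolescents and parents supply the responses and know their arm. Only the rater's share of the bias can be removed, and free text may still reveal the arm.

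Fourth, a reader might add the data monitoring committee, "consisting of clinicians working on the project", since "The members of the data monitoring committee will all have access to these interim analyses". Those monthly analyses are for harms, and nothing says that they are by arm or include the YODA. They do not support a claim of rating bias.

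Finally, capacity is tight. Recruitment {15} pauses when clinicians are fully booked, and the Discussion notes reliance on a small number of them. This is a real cost of the change.

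**Conclusion.** The point holds in limited form. ID-only analysis sheets cannot bring the design closer to assessor blinding for the YODA, because they act after the diagnosis is set. With no masked rater described, the YODA recovery outcome is open to rater bias.

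The weight is moderate. The Outcomes and Statistical methods sections rank YODA as secondary, and the trial is sized on SCAS, which no clinician rates. The abstract lists YODA as a primary measure, but that is a separate inconsistency and is not used here to raise the weight. YODA still carries the first hypothesis, so the matter should be put right.

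The 6% to 11% and 12% to 29% figures rest wholly on assumed recovery and tipping rates. They show that modest differential rating could matter. They do not show that it will occur.

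**What to change.** 1. Have the post-treatment and 3-month YODA responses rated from an export that omits the arm. The rater should be an already employed study psychologist who did not treat, assign or interview that family, for example one at the other centre.
2. Lock the post-treatment rating before the final video call.
3. Replace the sentence in {17a} with what is actually done: who rates the YODA, what they know of the arm, that families remain unblinded, and that free text may reveal the arm.
4. Where masked rating cannot be arranged, say plainly that YODA ratings are unblinded.

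The ratings have to be made in any case, so the cost is mainly reassigning them, preparing an arm-free export, and scheduling across centres with few clinicians. Step 3, and step 4 where it applies, need only a change of text.
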